## Abstract

**Introduction:**

Postherpetic Neuralgia (PHN) constitutes a severe sequelae following herpes zoster (HZ) Infection, and one of the most problematic issues is the treatment of cephalo-facial PHN in patients over 50 years of age, which severely affects the patient’s work mood, sleep and activities of daily living. The efficacy of conventional treatments for PHN remains unsatisfactory. Therefore, there is an urgent need for alternative approaches to explore simpler, more convenient, effective, and inexpensive treatment options in the clinical treatment of PHN. This trial aims to thoroughly evaluate the effectiveness and safety of EA as a therapeutic modality for individuals suffering from cephalo-facial PHN.

**Methods and analysis:**

The protocol outlines a double-center, randomized, and controlled trial design where both patients and assessors are blinded to the intervention being administered. The duration of the trial’s therapeutic intervention will span 4 weeks, followed by a 2-month observation period for monitoring any subsequent effects or outcomes. The 124 qualified individuals will be randomly allocated in a balanced 1:1 ratio to either the EA group or the drug group. All variables will undergo evaluation at the start of the study (week 0, baseline), during the treatment period at weeks 2 and 4, and during the follow-up period at weeks 8 and 12. The primary outcome is the Visual Analog Scale (VAS). Secondary outcomes include the Brief pain inventory-Facial scale (BPI-Facial), Pittsburgh Sleep Quality Index Scale (PSQI), Self-rating depression scale (SDS), Hamilton depression scale (HAMD), and Quality of Life Rating Scale (SF-36). The occurrence of any adverse reactions will be monitored and assessed throughout the duration of the trial.

**Conclusion:**

This study will preliminarily evaluate the efficacy and safety of electroacupuncture (EA) in the treatment of patients with postherpetic neuralgia (PHN).

**Ethics and dissemination:**

Ethical approval for this trial has been obtained from the Institutional Ethics Review Board of the Third Affiliated Hospital of Zhejiang Chinese Medical University (No. ZSLL-KY-2023-029-01) and Zhejiang Hospital (No. 2024-030-K). Before enrollment, participants will be required to sign a form of informed consent.

**Clinical trial registration:**

Identifier NCT06420778, https://clinicaltrials.gov/study/NCT06420778.

## Introduction

Postherpetic neuralgia (PHN) refers to a type of pain that persists for a duration of 1 month or longer, following the healing of an acute herpes zoster (HZ) rash (1). Epidemiological studies have shown that the occurrence rate of HZ in Europe, North America and the Asia Pacific region stands at 5 to 6 cases per 1,000 individuals per year and up to 30% of HZ patients develop PHN (2, 3). In China, the rate of PHN incidence is rising steadily each year, and the incidence increases with age (4). Clinical studies have found that PHN occurs mostly in the elderly, where the occurrence rate of PHN among patients aged over 50 can reach as high as 60 to 75%, which has a significant impact on both physical and mental well-being, as well as the overall quality of life (5, 6).

PHN, as a pain disorder that severely affects the quality of human life, faces many clinical challenges. One of the most problematic issues is the treatment of cephalo-facial PHN in patients aged 50 and above. The clinical challenges of cephalo-facial PHN in patients over 50 years of age are more daunting (7, 8), making the clinical symptoms of cephalo-facial PHN in patients over 50 years of age more complex and more difficult to treat. Therefore, this project will focus on patients over the age of 50 with cephalo-facial PHN for research.

Currently, the main clinical treatment options for PHN include drug therapy (9–11) and surgical treatment (12, 13) and alternative medicine (14, 15). Pregabalin has proven efficacy in the treatment of PHN (16) and is classified as a first-line clinical medication by guidelines (17); therefore, this study will use pregabalin as a control to investigate the clinical efficacy and safety of EA in patients with PHN. However, all of these treatment options have limitations. Studies have shown that 81.82% of patients with PHN still suffer from a similar degree of pain as before treatment, and their probability of adverse drug reactions is as high as 42.74% (18, 19). Although surgical treatment is effective for PHN, there is a greater risk of irreversible damage to the nerves and complications for patients over 50 years of age with cephalo-facial PHN (20). Therefore, there is an urgent need for alternative approaches to explore simpler, more convenient, effective, and inexpensive treatment options in the clinical treatment of cephalo-facial PHN over 50 years of age.

In the last decade, domestic and international clinical studies and evidence-based medicine suggest that complimentary medicine serves as an effective treatment option for PHN with minimal side effects (21–23). In the current acupuncture treatment program, most of the acupuncture treatments, such as milli-acupuncture, fire-acupuncture, and electro-acupuncture combined with other therapies are chosen (24, 25). Although the effectiveness of acupuncture in the therapy of PHN has been widely recognized, there is a variety of clinical therapies and a lack of uniform standardized treatment protocols (14, 26, 27). Previous clinical studies have focused more on PHN occurring in the body, and few acupuncture treatment protocols have been reported for PHN in the head and face.

Our scientific team has long been dedicated to the in-depth clinical practice and fundamental scientific research of acupuncture therapy in the field of relieving and managing neuropathic pain (28, 29). Previous studies conducted by us have shown that acupuncture, particularly EA, is efficacious in relieving neuropathic pain (30–34). It has been shown that the mechanism of EA analgesia is related to the interaction of a number of biologically active chemicals (e.g., opioids, serotonin, norepinephrine, etc.) in the periphery, spinal cord, and higher central nervous system (35). Therefore, EA may be one of the effective means of treating PHN of the head and face.

We has used EA to treat classical trigeminal neuralgia with satisfactory efficacy (36). Moreover, the treatment of PHN with EA has achieved preliminary efficacy in the clinic (37, 38), but no systematic study has been conducted, which is not conducive to the formation of a high-quality clinical expert consensus and hinders its clinical application and further promotion.

Therefore, this project intends to evaluate the efficacy of EA therapy for PHN patients from the perspective of clinical needs, using a randomized controlled trial with oral pregabalin as the control group, and adopting the evaluation index system acknowledged both domestically and internationally, as well as evaluating the safety and the impact on the patients’ quality of life, so as to further clarify the advantages of the program in the treatment of cephalo-facial PHN, in terms of immediate efficacy and aftereffect, and thus laying a foundation for further promotion and providing an innovative, evidence-based, and efficient approach for the clinical analgesia of PHN.

## Method and analysis

### Study design

This research is structured as a randomized, parallel-group, controlled clinical trial with patient-evaluator blinding. Based on the inclusion and exclusion criteria, patients with PHN of the head and face who met the requirements will be selected as the test subjects and randomly assigned to the EA group or the drug group. The efficacy of the subjects in the EA group and the drug group will be observed before treatment, immediately after the first treatment, after 2 weeks of treatment, after 4 weeks of treatment, at 1-month follow-up after the end of treatment and at 2-month follow-up after the end of treatment, respectively. The trial design is summarized in Figure 1, and the trial schedule for enrollment, treatment, and assessment is shown in Table 1. The reporting framework for this protocol adheres to the rigorous Standards for Reporting Interventions in Clinical Trials of Acupuncture (STRICTA) (39) as well as the comprehensive guidelines outlined in the Standard Protocol Items: Recommendations for Interventional Trials (SPIRIT) (40), ensuring a thorough and transparent documentation of the study.

**Figure 1 fig1:**
[figure not shown]
Flow chart of the study process. EA, electroacupuncture; VAS, Visual Analogue Scale; BPI-Facial, Brief Pain Inventory-Facial Scale; SDS, Self-Rating Depression Scale; HAMD, Hamilton Depression Scale; PSQI, Pittsburgh Sleep Quality Index Scale; SF-36, Short Form 36 Health Survey.

**Table 1 tab1:** Schedule of enrolment, treatments, and assessments.

Study period	Enrolment/baseline	Treatment period		Follow-up period	
Assessment point	1	2	3	4	5
Time	−2 Weeks to 0	2 Weeks ± 3 Days	4 Weeks ± 3 Days	8 Weeks ± 3 Days	12 Weeks ± 3 Days
Eligibility screening	√				
Demographic data	√				
Case data	√				
Inclusion criteria	√				
Exclusion criteria	√				
Informed consent	√				
Treatment		√	√		
Outcome assessment					
(1) VAS	√	√	√	√	√
(2) BPI-Facial	√	√	√	√	√
(3) SDS	√	√	√	√	√
(4) HAMD	√	√	√	√	√
(5) PSQI	√	√	√	√	√
(6) SF-36	√	√	√	√	√
Safety assessment (EA)		√	√		
Safety assessment (Medication)		√	√		
Adverse events	√				

EA, electroacupuncture; VAS visual analog scale, BPI-Facial Brief pain inventory-Facial scale; SDS Self-rating depression scale; HAMD Hamilton depression scale; PSQI Pittsburgh Sleep Quality Index Scale; SF-36, Short Form 36 Health Survey.

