### Intervention

Subjects will undergo either EA or pharmacotherapy. Both groups will receive treatment for a duration of 4 weeks, followed by a 8-week follow-up period.

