### Safety evaluation

Relevant safety indicators are recorded on the Subject Adverse Event Record Form by the acupuncturist at any time during treatment and follow-up:

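### Table 1 schedules the EA and medication safety assessments only at weeks 2 and 4, although the text says they are recorded through follow-up, by an acupuncturist with no described contact with patients after week 4

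*Protocol article*

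**What the plan says.** The text promises safety recording over the whole trial. The Abstract (Methods and analysis) states: "The occurrence of any adverse reactions will be monitored and assessed throughout the duration of the trial". The Safety evaluation section is more specific: "Relevant safety indicators are recorded on the Subject Adverse Event Record Form by the acupuncturist at any time during treatment and follow-up". That sentence introduces two lists, one of EA-related events and one of pregabalin reactions.

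Table 1 (Study design) has two rows that correspond to those lists, beginning "Safety assessment (EA" and "Safety assessment (Medication". Both are ticked at weeks 2 and 4 and blank at weeks 8 and 12. A third row, "Adverse events", shows a single tick, which falls in the enrolment/baseline column of the extracted text.

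The Intervention section fixes the time frame: "Both groups will receive treatment for a duration of 4 weeks, followed by a 8-week follow-up period". The last column of Table 1 is "12 Weeks ± 3 Days". Course of treatment gives 3 EA sessions a week for 4 weeks, 12 in all. Medication group describes pregabalin as that arm's sole treatment.

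**The concern.** Safety is a stated objective of the trial in the Abstract and again in the Conclusion, where EA is to be compared with medication. A comparison of harms needs the same events to be asked about, over the same period, in both arms and at both centres. A site that works from Table 1 would do the treatment-specific safety assessments twice, both by week 4. A site that works from the Safety evaluation section would continue to week 12. The two centres could then hold different data for the same period.

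The events at stake are those that appear or persist after treatment ends: a delayed local infection or abscess (both on the EA list), or a pregabalin reaction still present at week 4. If nobody asks about these at weeks 8 and 12, they cannot be reliably recovered later.

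The named recorder adds to the difficulty. Needling sessions bring the acupuncturist into contact with the EA arm for 4 weeks. The article describes no occasion on which that person sees a drug-arm patient, and none on which that person sees anyone during follow-up.

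**Working it through.** **Inputs.** From Table 1: visits at baseline and weeks 2, 4, 8 and 12, each post-baseline visit ±3 days, and the ticks in each row. From Intervention: 4 weeks of treatment and 8 of follow-up. From Course of treatment: 3 sessions a week for 4 weeks. From Safety evaluation: the recording period and the recorder.

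**Step 1, the plan's own time frame.** 4 + 8 = 12 weeks, which agrees with the last visit in Table 1.

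**Step 2, the ticks side by side.**

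| Row of Table 1 | Baseline | Wk 2 | Wk 4 | Wk 8 | Wk 12 |
|---|---|---|---|---|---|
| Each of the six outcome scales | yes | yes | yes | yes | yes |
| EA safety | – | yes | yes | – | – |
| Medication safety | – | yes | yes | – | – |
| Adverse events | one tick, span unclear | ? | ? | ? | ? |

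The blanks at weeks 8 and 12 in the two safety rows are unlikely to be an extraction fault, since the outcome rows just above them kept their ticks in those columns.

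**Step 3, the time not covered by the two safety rows.**
- Scheduled post-baseline visits with these assessments: 2 of 4.
- Share of follow-through after the last one: (12 − 4)/12 = 8/12 = 66.7%.
- With the ±3-day windows, the week-4 visit falls on days 25 to 31 and the week-12 visit on days 81 to 87. The share is then lowest at (81 − 31)/81 = 61.7% and highest at (87 − 25)/87 = 71.3%.

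**Step 4, the recorder.** 3 × 4 = 12 sessions, all within the 4 treatment weeks, so the article describes 0 sessions in weeks 5 to 12. The drug arm has no sessions at any time. The safety recording promised for follow-up thus has neither a tick in its own rows nor a recorder shown to be present.

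**Step 5, the adverse-event row under each reading.**
- If its tick is a merged cell spanning all visits, general adverse events are scheduled at weeks 8 and 12. Only the two treatment-specific rows then disagree with the Safety evaluation section.
- If its tick belongs to baseline alone, adverse events are scheduled only before treatment, and Table 1 has no safety tick after week 4.

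The merged headings for the treatment and follow-up periods were extracted in the same way, as one entry followed by blanks, so the first reading is quite possible. The extracted text cannot settle it. The mismatch in Step 2 remains under both readings.

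**Step 6, after correction.** With both safety rows also ticked at weeks 8 and 12, coverage is 4 of 4 post-baseline visits, and the share in Step 3 falls to 0%.

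**The case against.** The strongest reply is that the table and text can be read together. The two safety rows match the treatment row, which is also ticked at weeks 2 and 4. Several items on the EA list, such as a broken needle or fainting, can occur only at or soon after a session. General events have their own row, and two places in the text commit to recording beyond treatment. Patients do attend at weeks 8 and 12, and nothing says the acupuncturist is unavailable then.

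Part of this stands. The commitment in the text is clear, contact with patients in follow-up does exist, and session-bound events need no later tick. But the Safety evaluation section applies the follow-up period to both lists without distinction, and those lists include events that can arise or persist after week 4. That the acupuncturist could attend is not the same as a described contact, and for the drug arm none is described at all.

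Three stronger readings are tempting, and the documents support none of them:
- A reader might infer that no safety data of any kind are scheduled for two thirds of the trial. The unclear span of the adverse-event tick prevents that conclusion.
- A reader might apply the adverse-reaction rate quoted in the Introduction to the drug arm to count the events lost. That is a background figure for reactions of any timing, and says nothing about how many are still present at week 4.
- A reader might argue that the ±3-day window lets the week-4 assessment precede the last session. That depends on a session calendar and a day-counting convention that the article does not give.

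**Conclusion.** The point holds as a mismatch between the schedule and the text. The EA and medication safety assessments have no scheduled visit in the last 8 of 12 weeks (66.7%; 61.7% to 71.3% over the visit windows), while the text says these indicators are recorded through follow-up. The named recorder has no described role in the drug arm or after week 4.

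This rests on the tick positions of the two safety rows being as extracted, which the intact outcome rows support. It does not rest on the adverse-event row, and it does not show that all safety collection ends at week 4. How many events would be missed cannot be estimated from the article. Randomisation, the primary outcome and the efficacy analyses are unaffected. What is affected is whether the whole-trial comparison of harms that the article describes can be obtained in both arms.

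**What to change.** Reconcile Table 1 with the Abstract and the Safety evaluation section:

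1. Tick both safety rows at weeks 8 and 12.
2. Make the adverse-event row explicitly cover every post-baseline visit (weeks 2, 4, 8 and 12).
3. Have the staff who already conduct the week 2, 4, 8 and 12 assessments record adverse events in both arms. The acupuncturist can still record what happens during a session.

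If safety is meant to be collected only during treatment, narrow the statements in the Abstract and Safety evaluation instead, and limit the safety conclusion to the 4-week treatment period.

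The cost is a table correction and one extra form at two visits that already take place. One precaution: the Blinding section keeps those who record outcomes unaware of the group, and questions about needling or drug reactions can reveal it. The form should therefore be completed after the outcome scales at each visit.

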### Participant enrollment

Participants are being recruited mainly from the Third Affiliated Hospital of Zhejiang Chinese Medical University and Zhejiang Hospital. Subject recruitment is carried out through multiple channels, with researchers focusing on following up with specialty outpatient clinics and regular screening of hospitalized patients, and active communication with patients. In addition, measures such as paper media and WeChat are regularly taken to recruit for the whole society.

### Eligibility criteria

Expert physicians will base their diagnosis of PHN on a comprehensive assessment that includes the patient’s medical history, reported symptoms, the visible characteristics of distinctive lesions, and their distribution along a single dermatome. The specific criteria for eligibility are outlined below.

#### Inclusion criteria

Meets the diagnostic criteria in the 2016 Chinese Expert Agreement on Diagnosis & Treatment of PHN (41);History of herpes zoster of the head and face with healed and resolved head and face lesions, neuralgia symptoms persisting ≥1 month after lesion healing, baseline facial pain profile score ≥4, and abnormal sensation and pain sensitivity of the skin around the lesions;50 ≤ Age≤80 years, gender not limited;Consciousness, pain perception and discrimination, able to complete fundamental communication; andParticipants who have willingly given their informed consent to join this research.

#### Exclusion criteria

Herpes zoster occurs on the perineum, or in special types such as visceral shingles, meningeal shingles, and generalized shingles;Those who take a daily oral pregabalin dose of less than 0.2 g or more than 0.6 g for analgesia prior to inclusion;Patients who have had a serious adverse reaction to taking Prevacid, are allergic to acupuncture, or fall within the range of contraindications to electroacupuncture;Those who have a combination of severe heart, liver, or kidney damage, epilepsy, head injury, or other major illnesses such as cognitive dysfunction, aphasia, or psychiatric disorders, and who are unable to cooperate with treatment;Comorbidity with poorly controlled hypertension and diabetes mellitus;Patients who are pregnant or breastfeeding; andPatients who are participating in other studies and have been enrolled in other clinical studies patients within the past 3 months.

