#### Medication group

In this group, participants undergo treatment through the oral ingestion of pregabalin capsules (specification: 75 mg*8 capsules, manufactured by Pfizer Pharmaceutical Co., Ltd.) only, 150 mg each time, twice a day, for 4 consecutive weeks.

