## Conclusion

In summary, this research protocol is a multicenter, randomized controlled trial with blinding of both patients and assessors. The objectives are to evaluate the effectiveness and safety of EA compared with medication; and to clarify whether EA in the treatment of cephalo-facial PHN has a clear and stable advantage over oral pregabalin alone in terms of improvement in mood, quality of sleep, and quality of life. This finding will provide new scientific and effective ideas for the clinical treatment of PHN.

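### Patients still in pain on 0.2–0.6 g/day pregabalin may be randomised against pregabalin itself; this can lower the control response and may favour EA, by an amount that cannot be computed

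*Protocol article*

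**What the plan says.** - **Exclusion criteria:** "Those who take a daily oral pregabalin dose of less than 0.2 g or more than 0.6 g" for pain relief before inclusion are excluded. Users between 0.2 and 0.6 g/day are therefore eligible.
- **Inclusion criteria:** "baseline facial pain profile score ≥4" is required. The scale is not named as the VAS.
- **Medication group:** controls take pregabalin only, "150 mg each time, twice a day, for 4 consecutive weeks".
- **Intervention:** each participant receives one of the two treatments, EA or drug. The sections on EA treatment do not say what happens to pregabalin that a patient is already taking.
- **Sample size estimation:** the sizing endpoint is the proportion with VAS of 2 or less after 4 weeks. The planned rates are 91% for EA, from the team's own preliminary observation, and 74.4% for pregabalin, from the literature.
- **Conclusion:** the aim is to learn whether EA "has a clear and stable advantage over oral pregabalin alone".
- **Statistical analysis:** between-group comparisons use t-tests, chi-squared tests and rank tests. No covariate is named.

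**The concern.** A patient who takes an admissible dose of pregabalin and still scores 4 or more may be someone whose pain the drug has not controlled. Such a patient in the control arm gets the same drug again, while one in the EA arm gets something new. If prior users respond less well to more pregabalin than patients new to it, the observed control rate falls below the planned one, and the difference may widen in favour of EA.

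What is at stake is the meaning of a positive result. The stated aim is superiority over pregabalin. If a sizeable part of the sample already had pain on pregabalin, the result answers a narrower question: how EA compares with pregabalin in a mix of patients, some of whom have persistent pain despite it.

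The exclusion criterion itself can also be read in two ways. Taken literally, 0 g/day is less than 0.2 g/day, so non-users are out and every participant is a prior user. Taken as a rule for users only, non-users and users of 0.2–0.6 g/day are mixed. Under both readings, users with pain of 4 or more can enter.

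**Working it through.** **Step 1. Dose.** Control dose = 2 × 150 mg = 300 mg = 0.3 g/day, inside the 0.2–0.6 g/day window. For an admitted user, allocation to control is thus an increase (from below 0.3 g), no change (at 0.3 g) or a decrease (from above 0.3 g).

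**Step 2. The plan's own figures.** Planned difference = 0.91 − 0.744 = 0.166. The stated 62 per group does not follow from the stated inputs: one-sided 0.025, 80% power and these rates give 81 per group before dropout and 81/0.8, rounded up to 102, after it. That is a separate matter, and nothing below depends on it. What matters here is that 74.4% carries no stated link to patients already in pain on the drug.

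**Step 3. Control rate in a mixed population (illustration only).** Let f be the share of prior users and r their response rate on control. Neither is in the article. Assumed: f = 0.25 or 0.5, r = 0.2 to 0.4, and 0.744 in everyone else.

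Control rate = (1 − f) × 0.744 + f × r

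| f | r | Control rate | Shortfall from 0.744 |
|---|---|---|---|
| 0.25 | 0.2 | 0.558 + 0.050 = 0.608 | 0.136 |
| 0.25 | 0.4 | 0.558 + 0.100 = 0.658 | 0.086 |
| 0.5 | 0.2 | 0.372 + 0.100 = 0.472 | 0.272 |
| 0.5 | 0.4 | 0.372 + 0.200 = 0.572 | 0.172 |

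Under the literal reading of the exclusion criterion f = 1, and the control rate is simply r; the 74.4% then describes nobody in the trial.

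**Step 4. From shortfall to shift in the comparison.** The shortfall is measured against a planning figure. It is not yet a shift in EA minus control. Let e be the EA response rate in prior users and 0.91 the rate in everyone else. Then:

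Shift in (EA − control) = f × [(0.744 − r) − (0.91 − e)]

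- If EA response in prior users stays at 0.91, the shift equals the whole shortfall and favours EA.
- If EA response falls by the same amount as control response, the shift is zero.
- If EA response falls by more, for instance because existing pregabalin is stopped in that arm, the shift goes against EA.

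The article gives none of f, r or e, so neither the size nor the sign can be fixed.

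**The case against.** The strongest reply has four parts.

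1. **Randomisation follows eligibility.** Prior users fall in both arms in expectation. A reader might infer that the control arm is enriched for drug failures, or that an EA win could be pure selection. The documents do not support this: any enrichment is of the trial population. A difference arises only if prior users respond differently to the two treatments, which is a real contrast in the patients enrolled. This stands. The problem is one of interpretation and of the population to which the result applies.

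2. **The direction is not given.** The Intervention section points to EA replacing the drug. Stopping 0.2–0.6 g/day in the EA arm could act against EA while controls still receive 0.3 g/day. This stands, and it rules out reading the shortfalls in the table as a built-in EA advantage. It also weakens the inference that the contrast cannot be identified at all: the mention of pregabalin alone in the Conclusion can simply echo the description of the control. What remains open is how existing pregabalin is handled in the EA arm.

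3. **Drug failure is inferred.** The criterion speaks only of use before inclusion. It gives no duration, and the pain score is not said to be taken on a stable dose. This stands, so the exact wording is that these patients may have persistent pain on the drug.

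4. **An article condenses.** Washout, concomitant medication and baseline medication fields may be in the full protocol; Table 1 already lists case data at baseline. Their absence is not the point. The point rests on the printed eligibility window, the printed comparator and the printed claim.

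A reader might also set the Introduction's statement that "81.82% of patients with PHN still suffer from a similar degree of pain as before treatment" against the 74.4%. That sentence follows a remark about the limits of all treatment options and is tied neither to pregabalin nor to VAS of 2 or less, so it is no contradiction.

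**Conclusion.** The point holds in a limited form and should be fixed. As printed, the criteria admit users of 0.2–0.6 g/day pregabalin with a pain score of at least 4, and only the control arm is re-treated with that drug. This can lower the control response below 74.4% and may favour EA. Nothing in the article offsets it.

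With assumed shares of 25% or 50% prior users and an assumed 20–40% control response among them, the control rate would be 61–66% or 47–57%. These shortfalls of 9–14 or 17–27 points can be set beside the planned difference of 16.6 points, but they move the comparison towards EA only to the extent that EA response in the same patients falls by less. The true size and net direction are unknown.

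**What to change.** 1. Reconcile the Exclusion criteria, Intervention, Medication group and Conclusion sections on prior and current pregabalin in both arms: whether non-users are eligible, and what happens to existing pregabalin after randomisation. Which dose or clinical rule applies is for the sponsor; none is proposed here.
2. Record prior pregabalin use, dose and duration among the baseline case data.
3. Include prior use (yes/no) as a covariate in the primary analysis: logistic regression for the proportion with VAS of 2 or less, or analysis of covariance if the VAS score is analysed. If reconciliation shows that all participants are prior users, this and the next item fall away.
4. Report the EA–control difference by prior use. The covariate handles chance imbalance and gains precision; only the separate differences show whether the result depends on prior use.
5. Limit any conclusion on superiority over pregabalin to the population actually enrolled, and do not present 74.4% as the expected control rate for current users still in pain.

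**Cost.** One clarified criterion, a few baseline fields, one covariate and a narrower claim. Subgroup estimates will be imprecise: with 62 per arm and half of them prior users (31 per arm), the 95% half-width at the planning rates is 1.96 × √[(0.744 × 0.256 + 0.91 × 0.09)/31] = 0.18, wider than the planned 0.166. Recruitment is described as under way, so changing eligibility or adding a stratification factor would cost more and is not asked for here.

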#### Discontinuation criteria

A physician responsible for diagnosis assesses exacerbations of PHN occurring during the study, and when a patient experiences facial pain symptoms that persisted despite acupuncture treatment, as indicated by a VAS score exceeding 8, the physician evaluates the severity and subsequently discontinues the study;The specialist assesses the occurrence of significant adverse reactions during the study to make a decision on whether to proceed or discontinue the research;Participants who encounter severe complications or illnesses during the study that necessitate urgent medical attention; andParticipants who have additional reasons that prevent them from continuing with this study.

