### Randomization and allocation concealment

The envelope randomization method will be used for randomization. Upon meeting both the inclusion and exclusion criteria, subjects will be enrolled into the study. The randomization personnel or clinical researchers will randomize them based on the pre prepared patient grouping envelopes. The randomization protocol for this study will be generated by the Clinical Evaluation Center at the subject’s institution, and this person will be not involved in the statistical analysis of this project. The randomization scheme for this study and the individual parameters set in the process of generating that scheme are collectively referred to as the blind bottom, which is sealed and signed by the person generating the randomization scheme and kept by a dedicated subject matter manager not involved in this project. Participants in subgroups are not involved in the statistical analysis of data. The evaluation of the efficacy indicators will be collected and organized by a person who is unaware of the subgroups, with a triple separation of the researcher, the acupuncture operator, and the statistician.

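### An exclusion criterion names Prevacid where pregabalin is evidently meant, so as written nothing excludes a past serious reaction to the control drug

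*Protocol article*

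**What the plan says.** The third exclusion criterion (protocol article, Exclusion criteria) begins: "Patients who have had a serious adverse reaction to taking Prevacid". It goes on to allergy to acupuncture and contraindications to electroacupuncture.

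The control treatment is pregabalin. The Introduction says that "this study will use pregabalin as a control to investigate the clinical efficacy and safety of EA in patients with PHN". Under Medication group, "participants undergo treatment through the oral ingestion of pregabalin capsules", at a dose of "150 mg each time, twice a day, for 4 consecutive weeks". The safety section lists the adverse reactions to be recorded for pregabalin and for no other drug.

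One exclusion criterion does name pregabalin: "Those who take a daily oral pregabalin dose of less than 0.2 g or more than 0.6 g for analgesia prior to inclusion". It concerns prior dose.

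The eligibility list is the gate to the trial (Randomization and allocation concealment): "Upon meeting both the inclusion and exclusion criteria, subjects will be enrolled into the study".

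**The concern.** The third criterion joins a drug reaction to acupuncture allergy and electroacupuncture contraindications. It is evidently meant to keep out patients who cannot safely receive one of the two trial treatments. The electroacupuncture half does that. The drug half names a product that nobody in the trial receives, so the intended protection for the pregabalin arm is missing from the text.

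What is at stake is the safety of a small group. A patient known to have had a serious reaction to pregabalin could satisfy every listed criterion and, under 1:1 allocation, have an even chance of being given the drug again for 4 weeks.

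**Working it through.** The core check is a reading of the text. The arithmetic only indicates scale.

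**Step 1: which drug the trial uses.** Pregabalin is the control drug in the Introduction, Medication group, Safety evaluation, Sample size estimation and Conclusion. Prevacid occurs once, in the third exclusion criterion.

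**Step 2: whether another criterion covers a past pregabalin reaction.** The seven exclusion criteria concern, in order:

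1. zoster site or special type
2. prior pregabalin dose
3. serious reaction to Prevacid, acupuncture allergy, or electroacupuncture contraindication
4. severe organ disease, epilepsy, head injury and other major illness
5. poorly controlled hypertension and diabetes
6. pregnancy or breastfeeding
7. participation in other studies

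One mentions pregabalin, for dose only. One mentions a drug reaction, to Prevacid only. None mentions a past reaction to pregabalin, and the inclusion criteria do not either.

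**Step 3: whether the dose criterion closes the gap indirectly.** It can be read in two ways.

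- *It applies only to current users.* A patient who stopped pregabalin after a serious reaction takes no dose, so the criterion does not touch that patient, who passes.
- *A dose of 0 g counts as below 0.2 g.* That patient is excluded by dose. Only people currently taking 0.2 to 0.6 g/day are eligible, and few of them are likely to have had a serious reaction.

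The text does not say which is meant.

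**Step 4: whether a later safeguard helps.** Under Discontinuation criteria, "The specialist assesses the occurrence of significant adverse reactions during the study". This acts only once the patient has been exposed again.

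**Step 5: scale.** Inputs from the article are 124 patients, 62 per arm (Sample size estimation), and 2 × 150 = 300 mg/day (Medication group). The share *p* of otherwise eligible patients with a past serious pregabalin reaction is not given. The range below is an assumption. On the first reading in step 3, with the criterion applied literally:

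- expected number in the pregabalin arm = 62*p*
- chance of at least one = 1 − (1 − *p*)^62
- patients the corrected wording would turn away, both arms together = 124*p*

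| Assumed *p* | 62*p* | Chance of at least one | 124*p* |
|---|---|---|---|
| 0.5% | 0.31 | 26.7% | 0.62 |
| 1% | 0.62 | 46.4% | 1.24 |
| 2% | 1.24 | 71.4% | 2.48 |

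On the second reading, all three quantities are close to zero.

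**The case against.** The strongest reply is that this is a language slip in an English article about a trial run at two hospitals in Zhejiang. The text has other slips of the kind, such as the odd terms used for needle manipulation and for equality of variances. Screening staff probably work from a different document, and the article cannot show what that document says. The intended meaning is clear from the rest of the criterion. Trained clinicians who take a medical history are unlikely to randomise someone they know reacted badly to pregabalin. The percentages above rest on an assumed *p*, and they suppose that every such patient is approached, consents and is passed by the physician. Nothing in the trial's inference changes.

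Much of this stands. The slip is probably linguistic, the operative forms are unseen, and the percentages illustrate scale without being evidence of what will happen. But this is not detail left to a fuller document. The article states the criterion and names the wrong drug in it. A reader's ability to guess the intended drug, or a clinician's good sense, does not make the written rule correct. The Randomization section makes these criteria the condition for entry, so the word should be right.

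**Conclusion.** The criterion is wrong as written and should be fixed. That pregabalin was meant is an inference, but a strong one, because it is the only drug the trial gives.

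The practical exposure is unknown and probably small. It requires three things: that the operative documents carry the same word, that staff apply it literally, and that the dose criterion covers current users only. If all three hold, about 0.3 to 1.2 patients in the pregabalin arm would be expected for an assumed *p* of 0.5% to 2%. If non-users fall under the dose exclusion, the figure is near zero. No effect on the sample size, endpoint or analysis is claimed. The conclusion that the wording is wrong does not depend on how the dose criterion is read.

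**What to change.** - Replace Prevacid with pregabalin in the third exclusion criterion.
- As a separate clarification, state whether the 0.2 to 0.6 g/day criterion applies to patients who take no pregabalin.
- Confirm that the operative protocol, screening form and case report form at both centres name pregabalin. Re-check patients already enrolled only if those documents carry the same error.

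The cost is one word, one clause and a check of forms at two sites. At most a few candidates would be turned away (124*p*, or 0.6 to 2.5 for the assumed range). Recruitment can continue to 124, so this means slightly more screening and no loss of sample size.
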